**Fig 1 pone.0316333.g001:**
[figure not shown]
Contents for the schedule of enrolment, intervention and assessments according to SPIRIT requirement.

### Measures

Study results will be measured at multiple time points and changes from baseline to each time point will be assessed. The results included objective indicators such as weight, sex hormones, metabolism, and subjective indicators such as quality of life [42], sleep quality [43], and psychological status [44]. We will not interfere with the normal treatment of PCOS women throughout the trial period. Table 1 summarized the details of the collection of outcome indicators.

**Table 1 pone.0316333.t001:** Outcome measures and measurement methods.

Outcome Measure		Collection Method/Tool			Details	Measurement Time Points
Weight and BMI		Multi-frequency bioelectrical impedance analyzer IOI scanner			Each participant will be asked to take the measurements after fasting (or three hours after eating and drinking) and after emptying their bladder and bowels. Each participant will be asked to take the measurement on an empty stomach (or three hours after eating or drinking water) and after defecating. Participants will take off their shoes and socks during the measurement, and their weight and height will be measured by the multi-frequency bioelectrical impedance analyzer IOI (IOI, Seoul, Korea) scanner to calculate their BMI (weight kg/ height m squared, kg/m^2^).	Intervention: baseline, once a week Follou-up: once a month
Sex hormones		Chemiluminescence immunoassay analysis			Participants will have their sex hormones measured between the 2nd and 4th days of their menstrual cycle; for those with amenorrhea, the date is not restricted. They will fast for 12 hours before the test. The tests will be conducted using chemiluminescence immunoassay analysis.	Baseline, 4^th^ week, 8^th^ week, 12^th^ week
Metabolic parameters		Fasting blood tests			Fasting blood tests will be conducted to analyze glucose metabolism parameters (glucose, insulin, HOMA-IR, and HbA1c levels) and lipid profile (triglycerides, total cholesterol, and LDL/HDL cholesterol).	
Body composition		Multi-frequency bioelectrical impedance analyzer IOI scanner			The measurement requirements are the same as the anthropometry, the body composition will be assessed by the IOI scanner, including body fat (kg), muscle (kg), water (L), inorganic salts (kg), protein (kg).	
**Outcome Measure**	**Collection Method/Tool**			**Details**		**Measurement Time Points**
Scale	Pittsburgh Sleep Quality Index			The Pittsburgh Sleep Quality Index (PSQI) was used to rate participants’ sleep quality. It consists of 19 self-assessment entries and 5 other-assessment entries, in which the 19th self-assessment entry and 5 other-assessment entries are not involved in scoring. 18 entries form 7 components, each component is scored on a 0–3 scale, and the cumulative score of each component is the total PSQI score, which ranges from 0–21, with higher scores indicating poorer sleep quality.		Baseline, 4^th^ week, 8^th^ week, 12^th^ week
	SF-36			Sf-36 consists of eight dimensions: vitality (VT), mental health (MH), physiological function (PF), physiological function (RP), emotional function (RE), physical pain (BP), social function (SF), and general health (GH). The 8 dimensions get their own dimension score according to their own entry score, and the health change score is not included in the total score. The total quality of life score is the sum of eight dimensions, and the higher the total score, the better the quality of life.		
	Hospital Anxiety and Depression Scale			Hospital Anxiety and Depression Scale (HADS) was used to assess the degree of anxiety and depression of the participants, including two subscales, Hospital Anxiety and Depression Scale-Anxiety (HADS-A) and Hospital Anxiety and Depression Scale-Depression (HADS-D), with 7 entries each and a total of 14 entries. Higher scores indicate more severe anxiety or depressive symptoms.		
**Outcome Measure**			**Collection Method/Tool**		**Details**	**Measurement Time Points**
Compliance assessment			*Wechat* app		Compliance will be determined by the number of days participants adhere to the assigned dietary rules. Control group participants will be instructed to limit their caloric intake to the defined daily allotment, while TRE group participants will be consumed within designated mealtimes and meet daily calorie targets. We will employ a combination of methods to monitor compliance, including the use of food diaries and *Wechat* apps that can track meal times, calorie intake, and adherence to dietary rules. To improve participant compliance, each participant will be given a free physical examination and a food scale.	Intervention: baseline, once a week Follou-up: once a month
Safety assessment*			Asked by the investigator or voluntarily reported by the participant		Investigators will collect, record, and report all adverse events that occur during the trial period (beginning with the participant’s informed consent and ending with the participant’s last assessment, whether asked by the investigator or voluntarily reported by the participant). The participant’s symptoms, severity, onset and duration, treatment, and course of action will be recorded in the original data to evaluate their relevance to the trial intervention, and will be recorded in detail, signed and dated by the investigator. If serious adverse events occur during the clinical trial, the investigator will take appropriate treatment measures for the subjects and record them in the original data, and report them to the principal investigator of the trial center and the ethics committee within 24 hours. Researchers will carefully fill in the serious adverse event report form, and sign and date the report.	

*Safety indicators will include: the overall incidence of adverse events and the incidence of each adverse event; the severity and incidence of various types of gastrointestinal reactions, such as nausea and gastroparesis; the severity and incidence of hypoglycaemic events; early withdrawal due to adverse events; changes in vital signs; the severity and incidence of psychoneurological symptoms such as somnolence, anorexia, and other events.

### Data analysis

The Anderson-Darling method will be used to test the normality of continuous variable data. Continuous data will be expressed as M = xx.x, SD = xx.xx (for normal distribution) or median (with interquartile spacing) (for non-normal distribution). Statistical analysis will be performed for either the T-test (normal distribution) or the Wilcoxon rank test (non-normal distribution).

To account for the longitudinal nature of the data and to assess time and group effects, mixed-effects models will be utilized. These models will enable us to capture within-subject variability and more accurately estimate changes over time, particularly for secondary outcomes. Additionally, if time-to-event analysis is relevant (e.g., time to reach certain metabolic or hormonal targets), a Cox proportional hazards model will be included to examine the risk of achieving specific health milestones.

For the analysis of multiple dependent variables simultaneously, controlling for potential confounders such as age or baseline BMI, multivariate analysis of covariance (MANCOVA) will be considered. However, given the complexity and potential limitations (e.g., sample size), the feasibility of this analysis will be carefully assessed. Specifically, we acknowledge that the sample size may be a concern, and we will discuss why certain important factors for weight change (e.g., dietary intake, physical activity levels) were not controlled during sampling. These decisions may have been influenced by practical considerations such as the availability of data or the feasibility of collecting additional information. Despite these limitations, we will explore alternative statistical methods to address these concerns and ensure the robustness of our findings.

Structural equation modeling (SEM) will be explored to provide insights into the interdependencies between various outcomes, such as the relationship between metabolic parameters and psychological outcomes like anxiety or quality of life. A chi-square test for independence will be employed to analyze categorical data, such as compliance levels or adverse events. Repeated measures ANOVA with appropriate post-hoc testing will be utilized to clarify the timing and magnitude of changes, identifying significant differences between time points. Sensitivity analysis will be conducted to assess the robustness of the results by testing different model specifications or excluding outliers.

All statistical analyses will be performed using appropriate software (e.g., GraphPad Prism 8.0.1 or R, depending on the specific requirements of the analysis), and bilateral tests will be used for all results. Statistical significance will be determined at the P < 0.05 level. The intention-to-treat (ITT) population approach will be adopted to handle program non-adherence, ensuring that all randomized participants are included in the analysis according to their original group assignment. Missing data will be addressed using appropriate imputation methods, such as multiple imputation, to minimize bias and maintain the integrity of the statistical analysis.

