### Participants

#### Sample size

The study will enroll 96 overweight and obese women with PCOS, and the sample size is based on the estimation formula for the sample size required to compare the two sample means of the measurement data [13]:

$$N=\frac{2*{\left(Z_{1-\frac{\alpha }{2}}+Z_{1-\beta }\right)}^{2}*\sigma^{2}}{\delta^{2}}$$

N represents the sample size for each group. $Z_{1-\frac{\alpha }{2}}$ is the Z-score corresponding to the desired significance level (α). For a significance level of 0.05, $Z_{1-\frac{\alpha }{2}}$ = 1.96. $Z_{1-\beta }$ is the Z-score corresponding to the desired power (1 - β). For a power of 80%, $Z_{1-\beta }$ = 0.84. According to the reviewed literature [39], σ = 3.87, δ = 2.5kg. Considering a 20% to 25% dropout rate, the final sample size will be determined to be 48 participants per group, for a total of 96 participants.

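### The group test for weight and BMI is unadjusted and chosen by a normality pre-test, and no single primary analysis is named among the methods listed

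*Protocol article*

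**What the plan says.** All references are to the protocol article.

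- **Test rule.** Data analysis applies an Anderson-Darling test to continuous variables and continues: "Statistical analysis will be performed for either the T-test (normal distribution) or the Wilcoxon rank test (non-normal distribution". The Methods part of the Abstract repeats that the choice between the two tests follows the distribution. Neither test carries a covariate.
- **Mixed models.** The same section commits to mixed-effects models for the longitudinal data and for time and group effects. It adds that they will "more accurately estimate changes over time, particularly for secondary outcomes". The Abstract mentions them without that emphasis.
- **Other methods.** "Repeated measures ANOVA with appropriate post-hoc testing will be utilized to clarify the timing and magnitude of changes". A MANCOVA that could control for age or baseline BMI is only a possibility, subject to feasibility.
- **Use of baseline.** Measures says that change from baseline is assessed at each visit. Weight and BMI are measured weekly during the intervention (Abstract; Table 1).
- **Sizing.** Sample size uses the formula for comparing two means without covariates, with "σ = 3.87, δ = 2.5kg".
- **Error level and population.** "Statistical significance will be determined at the P < 0.05 level", two-sided. The analysis is by intention to treat, "ensuring that all randomized participants are included in the analysis", with multiple imputation given as an example for missing data.

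**The concern.** A t-test compares mean change in kilograms. A Wilcoxon test compares ranks and does not in general estimate a difference in means. If a pre-test on the trial's own data picks between them, the quantity the trial reports is not fixed in advance. As worded, the rule could also send weight one way and BMI the other, or change from one week to the next.

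The mixed model and the repeated-measures ANOVA can address the same weight data as well, and nothing says which result answers the primary question. Baseline weight, known for every woman, enters the committed group test only through the change score. Allocation is simple 1:1 with no stratification (Randomization and blinding), so adjusting for baseline would be worthwhile.

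At stake are a fixed answer in the units used for sizing, some precision, and protection against choosing among analyses after the results are seen.

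**Working it through.** **1. Reproduce the planned size.** Inputs from Sample size: z-values 1.96 and 0.84, SD 3.87, difference 2.5 kg.

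n = 2 × (1.96 + 0.84)² × 3.87² / 2.5² = 37.6, so 38 per arm. At 20% dropout, 38 / 0.80 = 47.5, rounded up to 48, which is the stated figure. At 25% dropout, 48 × 0.75 = 36 completers remain.

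Power = Φ(2.5 / (3.87 × √(2/n)) − 1.96), which is 80.4% at n = 38 and 78.3% at n = 36. These are powers for an unadjusted comparison of means.

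**2. What baseline adjustment adds.** The article does not say whether 3.87 is the SD of change or of final weight, and it gives no correlation. Assume that it is the SD of change, that variances are equal at baseline and follow-up, and that the two weights correlate ρ. Then

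- variance of change = 2σ²(1 − ρ), with σ the SD of body weight;
- residual variance after adjustment = σ²(1 − ρ²);
- ratio of the two = (1 + ρ)/2, so residual SD = 3.87 × √((1 + ρ)/2);
- implied body-weight SD σ = 3.87 / √(2(1 − ρ)).

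| ρ (assumed) | SD factor | Needed n per arm | Power at 38 | Power at 36 | Implied weight SD (kg) |
|---|---|---|---|---|---|
| unadjusted | 1 | 38 | 80.4% | 78.3% | – |
| 0.95 | 0.987 | 37 | 81.4% | 79.3% | 12.2 |
| 0.9 | 0.975 | 36 | 82.4% | 80.3% | 8.7 |
| 0.8 | 0.949 | 34 | 84.3% | 82.4% | 6.1 |
| 0.7 | 0.922 | 32 | 86.3% | 84.4% | 5.0 |

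The last column shows which rows are credible. Inclusion criteria admit BMI from 24 kg/m² with no upper limit, so a weight SD of only 5 kg looks too narrow. The gain is therefore more likely 1 to 2 points than 6. Any further gain from modelling all the weekly weights cannot be computed without the within-person correlations.

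**3. What the pre-test does.** Simulation with 38 per arm and 6,000 trials per scenario. Every distribution was scaled to SD 3.87. The Anderson-Darling test was run at 5% in each arm, and the Wilcoxon test was used if either arm was rejected.

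| Shape (assumed) | Switches to Wilcoxon, no effect | Type I error, two-stage | Power at 2.5 kg, two-stage | Power at 2.5 kg, t-test always |
|---|---|---|---|---|
| Normal | 10.2% | 5.3% | 79.6% | 80.0% |
| Log-normal | 94.0% | 4.8% | 90.9% | 79.3% |
| t, 4 df | 57.8% | 4.8% | 88.9% | 80.3% |

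Error stays near nominal and power does not suffer. But even with exactly normal data about one trial in ten would be analysed on ranks instead of means. The simulation moves the whole distribution by 2.5 kg, which favours the rank test. It does not cover arms that differ in shape or spread.

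**The case against.** The defence has real force, and several stronger readings a reader might infer are not supported.

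- **That the t-test or Wilcoxon test is the declared main comparison.** The article never says so. The order of the text and the sizing formula make it a natural inference, but only an inference.
- **That the mixed model is reserved for secondary outcomes.** The wording gives emphasis, not exclusion, and the Abstract has no such limit. The weekly weights may well be modelled.
- **That baseline is ignored.** Change scores remove the baseline level. What remains is the association between baseline and change, hence the small gain above.
- **That the pre-test inflates type I error.** It does not in the simulated cases. Taking the smaller of the two p-values would give about 6.1% to 6.4%, but the article does not plan that.
- **That repeated-measures ANOVA conflicts with intention to treat by needing complete series.** Multiple imputation is foreseen and would complete the series. The ANOVA's stated purpose is to describe change between time points, so it is not shown to be a rival primary analysis.

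It can also be said that an article leaves model detail to a full protocol or analysis plan. That holds for covariance structure and exact terms. It does not cover the test rule, which this article states outright and which makes the primary comparison depend on the data.

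**Conclusion.** The point holds in this limited form: the group test stated for the primary outcomes is unadjusted and selected by the data, it sits beside other methods with no order of precedence, and no covariate adjustment is committed. The main harm is that the estimand may move from a mean difference in kilograms to a rank comparison. The lost precision is secondary: about 1 to 6 power points at 38 per arm for correlations of 0.95 to 0.7, probably 1 to 2.

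These sizes rest on reading 3.87 as the SD of change, on equal variances, on the assumed correlations and on the simulated shapes. The case for change does not rest on error inflation. It should be made because it is nearly free.

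**What to change.** For both weight and BMI, name as primary one mixed model for repeated measures on the weekly values, with arm, week, arm-by-week and the baseline value as covariate. Report the arm contrast with its 95% CI at the end of the 12-week intervention. First reconcile that time point with the Objective in the Abstract, which speaks of effects at six months.

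Drop the normality gate. Keep the Wilcoxon test as a stated sensitivity analysis, and repeated-measures ANOVA, if at all, as descriptive only.

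The cost is a wording change and slightly more programming. The weekly weights are already collected, R is already among the software options, and the sample size need not change. The amendment should be made before anyone sees outcome data by arm.

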## Abstract

**Background:**

Time-restricted eating (TRE) manages weight effectively, but choosing how long and what time window remain debatable. Although an 8:00 a.m. to 16:00 p.m. time frame is reported to show positive results in most weight loss trial, its safety and efficacy in overweight and obese women with polycystic ovary syndrome (PCOS) is uncertain. This randomized controlled trial is conducted to evaluate the safety and efficacy of TRE in specific populations.

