Although TRE has shown good effects such as diabetes, metabolic syndrome, and cardiovascular diseases [32,33], there are limited studies on it in overweight and obese women with PCOS. TRE has shown certain weight loss effects in anovulatory PCOS women [34]. However, due to the small sample size (n = 25), neglecting the impact on ovulation and the non-randomized design, the reliability of the conclusion remains to be verified.

Significant effects of TRE become apparent after 4 weeks of continuous implementation, with the potential for greater weight loss over an extended intervention period of 12 weeks [35,36]. To thoroughly investigate TRE’s impact on this specific demographic, a 12-week randomized controlled trial will be carefully planned. In the trial design, we will combine international health guidelines with the dietary habits of Chinese individuals, ultimately selecting 8:00 a.m. to 16:00 p.m. as the optimal feeding window [37,38]. In addition, to ensure the validity of the trial, calorie intake will be appropriately restricted. Following the conclusion of the trial, a 3-month follow-up will be conducted to further evaluate the long-term effects and safety of TRE. Through such an approach, we aim to comprehensively and precisely evaluate TRE’s efficacy in this population, offering effective, practical, and scientific dietary management strategies to these women, thus helping them achieve positive metabolic health.

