## Discussion

There is extensive literature suggesting that being overweight and obese can exacerbate symptoms and complications in women with PCOS [45,46]. Weight loss of 5% to 10% is sufficient to improve clinical symptoms such as menstrual disorders and insulin resistance [2]. Given the increased prevalence and severe consequences of overweight and obesity in PCOS, traditional dietary weight loss strategies suffer significant limitations. As TRE is an emerging strategy that can compensate for the shortcomings of traditional dietary interventions and can treat obesity and improve adult metabolism, we will conduct a randomized controlled trial to evaluate the safety and effectiveness of TRE interventions in overweight and obese women with PCOS.

There are strengths of the study protocol. Firstly, we will improve our study protocol and develop a more rigorous randomization, control design and more scientific sample sizes. Our study will adopt a randomized controlled study design, which can effectively prevent selection bias and improve the comparability between groups to ensure the objectivity and accuracy of research results. In the selection of sample size, we will choose a more appropriate calculation formula in order to get more scientific and effective results. Secondly, in terms of outcome measurement, specific indexes of overweight or obese PCOS will be selected to explore the effects of this dietary pattern on metabolic characteristics and even reproductive health. Data will be collected from the same individual at three different time points, which can eliminate inter-individual variance in the results. Thirdly, we combined evidence-based strategy and Chinese eating habits to choose the best eating window, which can improve the compliance of the trial and obtain significant results as well.

However, there are some limitations to our study. First, repeated questionnaires during the trial may induce bias. To avoid memory overlap due to insufficient time intervals, each questionnaire measurement interval will span six weeks, and all participants will complete offline surveys with uniform guidance provided by researchers. Second, this study does not guarantee blindness for study participants, thus introducing potential uncertainty. Nevertheless, we aim to mitigate this through blinded outcome assessors and data analysts.

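### Safety is a stated purpose, but the only comparative method named for adverse events is a chi-square test at P<0.05, which cannot support a safety statement for uncommon events at 48 per arm

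*Protocol article*

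**What the plan says.** Three places give safety as a purpose. The Abstract (Background) says "This randomized controlled trial is conducted to evaluate the safety and efficacy of TRE in specific populations". The Introduction describes follow-up after the trial "to further evaluate the long-term effects and safety of TRE". The Discussion restates the purpose as being "to evaluate the safety and effectiveness of TRE interventions in overweight and obese women with PCOS". The Abstract's Objective lists weight, metabolic, reproductive and quality-of-life effects and does not mention safety.

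The footnote to Table 1 (Measures) lists the safety indicators. They include "the overall incidence of adverse events and the incidence of each adverse event", gastrointestinal, hypoglycaemic and psychoneurological events, and "early withdrawal due to adverse events; changes in vital signs".

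The Data analysis section names the method for adverse events: "A chi-square test for independence will be employed to analyze categorical data, such as compliance levels or adverse events". It adds that "bilateral tests will be used for all results" and "Statistical significance will be determined at the P < 0.05 level".

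The Sample size section uses a standard deviation of 3.87, a difference of 2.5 kg, 80% power and 20-25% dropout, and arrives at 48 per group. It does not consider adverse events, and the article gives no expected event rate for either arm.

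**The concern.** The aim and the named method do not match. A chi-square test of independence asks whether the data contradict equal risk. When it does not reject, it says nothing about how large an excess remains possible, and that is what a reader of a safety result needs to know. In a trial sized for a continuous efficacy outcome, the test will often fail to reject for uncommon events even when the risk is materially higher. The listed event types, such as hypoglycaemia or gastroparesis, may well be uncommon, although the article does not say.

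At stake is what the trial can say about the tolerability of a daily 16-hour fast in a population for which it calls safety uncertain. If the report gives only P values for harms, that question stays largely unanswered.

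**Working it through.** **Inputs from the article.** 48 per group, 1:1 allocation, two-sided alpha 0.05, chi-square test, 20-25% dropout. All randomized women are analysed in their assigned group. Event rates are not given, so those below are assumptions shown over a range.

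**The plan's own figure.** n = 2(1.96 + 0.84)² × 3.87² / 2.5² = 37.6, rounded up to 38 per group. With 20% dropout, 38/(1 − 0.20) = 47.5, rounded up to 48. The stated size reproduces, and it depends on weight only.

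**Power of the named test.** With x₁ and x₂ women affected among n per arm, and p̄ = (x₁ + x₂)/(2n), the uncorrected statistic is

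X² = (x₁/n − x₂/n)² / [p̄(1 − p̄) × 2/n], rejecting when X² > 3.84.

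Exact power is the sum of the two binomial probabilities over all pairs (x₁, x₂) that reject. The miss rate is one minus power.

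| Assumed rates, control vs TRE | Power, 48 per arm | Miss rate, 48 per arm | Power, 36 per arm |
|---|---|---|---|
| 5% vs 10% | 17% | 83% | 13% |
| 10% vs 20% | 29% | 71% | 22% |
| 15% vs 30% | 43% | 57% | 33% |
| 20% vs 40% | 59% | 41% | 47% |
| 5% vs 15% | 41% | 59% | 32% |
| 10% vs 30% | 72% | 28% | 58% |
| 15% vs 45% | 91% | 9% | 82% |

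The 36-per-arm column (48 × 0.75) is the pessimistic case in which dropouts contribute nothing. Women who leave still contribute events recorded before they leave, so 48 is the fairer basis.

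At 48 per arm a doubling is missed more often than not up to a control rate of about 15%. A tripling is missed more often than not from 5%, but not from 10%.

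**Size needed.** By the normal approximation, 80% power for a doubling needs 435, 199 or 82 per arm at control rates of 5%, 10% or 20%.

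**What a non-significant result leaves open, at 48 per arm.**
- 5/48 on TRE against 2/48 on control: X² = 1.39, P = 0.24. The difference is 10.4% − 4.2% = 6.3 points, with a Newcombe 95% CI from −5 to +18 points.
- 5/48 in each arm: P = 1, yet the 95% upper limit of the risk ratio is exp[1.96 × √(2/5 − 2/48)] = 3.2.
- No events in 48: the one-sided 95% upper bound on the risk is 1 − 0.05^(1/48) = 6.1%.

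**Would an exact test help?** The uncorrected chi-square keeps its type I error at or below about 6% for common rates of 2% to 20% at 48 per arm. Fisher's exact test raises the miss rate to 94% for 5% vs 10% and to 77% for 5% vs 15%. Sparse cells are therefore not the main difficulty, and changing the test would make missed harms more likely.

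**The case against.** A chi-square test for adverse events is conventional in a trial powered on efficacy, and the article does not rule out confidence intervals. Their format, and any margin, are details that an analysis plan could hold, and that plan is not shown. This stands as far as omission goes: the absence of a margin or interval is not itself an error. The point rests on the method the article does name, set against the purpose it states.

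A reader might infer that a non-significant test will be reported as proof of safety. The document does not support that. No section states such a rule.

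A reader might also infer that the trial would usually miss any doubling or tripling of harm. The table shows otherwise: a tripling from 10% and a doubling from 20% are detected more often than not at 48 per arm. Overall adverse-event incidence could lie in that range, because the weekly calls ask about hunger, dizziness and mood.

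Nor is the chi-square test the whole safety assessment. Vital signs are continuous and fall under the other named methods. Severity, relatedness, withdrawals and serious events are also recorded. Finally, the formal Objective omits safety, so it would be too strong to call safety half of the trial's question.

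**Conclusion.** The point holds in a limited form. Safety is a stated purpose, the sample size rests on weight, and the only comparative method named for adverse events cannot support a statement that time-restricted eating is safe with respect to uncommon events. For control rates of about 5-10%, power to detect a doubling is 17-29%; for a tripling from 5% it is 41%. For doublings the weakness extends to a control rate of about 15%. It does not extend to every doubling or tripling.

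These figures assume 48 per arm, the uncorrected chi-square test and event rates that the article does not supply. Misreading P>0.05 as safety is a risk, because P<0.05 is the only criterion given; it is not something the protocol commits to. The change is worth making because it replaces a named method with a better one at almost no cost.

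**What to change.** In Data analysis, take adverse events out of the chi-square sentence as the main method. For overall adverse events and for each event type in the Table 1 footnote, specify:

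- the number and percentage of participants with at least one event in each arm;
- the risk difference, TRE minus control, with a Newcombe/Wilson 95% confidence interval;
- a safety statement based on the upper confidence limit, that is, the largest excess the data do not exclude;
- a sentence that P>0.05 is not evidence of safety.

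A chi-square P value may stay as a secondary result. It should not be replaced by Fisher's exact test to address missed harms, since that lowers power further.

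The cost is a revised paragraph and a little extra output, with no additional participants or procedures. The downside is a more modest safety claim: the trial would describe tolerability with stated precision.

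### Compliance is measured as a count of adherent days, but the only test linked to it is a chi-square on levels, which loses power for no stated gain

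*Protocol article*

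**What the plan says.** Under Measures, the compliance row of Table 1 in the protocol article reads: "Compliance will be determined by the number of days participants adhere to the assigned dietary rules". The row is assessed weekly during the intervention, and Study design and ethics sets the intervention at 12 weeks. Each woman therefore has a count between 0 and 12 × 7 = 84 days.

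The same row defines an adherent day by arm. Control participants must stay within their daily calorie allotment. TRE participants must meet calorie targets and also eat within the set hours.

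Data analysis then says: "A chi-square test for independence will be employed to analyze categorical data, such as compliance levels or adverse events". No other sentence there names compliance together with a test. For continuous data the section says: "Statistical analysis will be performed for either the T-test (normal distribution) or the Wilcoxon rank test (non-normal distribution"). It also provides mixed-effects models for longitudinal data, particularly for secondary outcomes. The general rules are "bilateral tests will be used for all results" and "Statistical significance will be determined at the P < 0.05 level".

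**The concern.** The scale on which compliance is collected does not match the scale on which it is tested. A chi-square test of independence on grouped days treats women within a level as identical, uses neither the distance between levels nor (with three or more) their order, and gives no difference in days. It also needs one independent observation per woman, so the weekly records have to be collapsed before it can be applied.

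What is at stake is modest but real. The Introduction lists adherence among the difficulties of existing diets, and the Discussion counts it as a strength that the chosen eating window can improve compliance. A non-significant chi-square on coarse levels could be misread as equal adherence when the day counts differ.

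**Working it through.** **Inputs.** Two-sided α = 0.05 comes from Data analysis. From Sample size come "σ = 3.87, δ = 2.5kg", 80% power and 48 women per group. The article gives no effect, SD, number of levels or cut-point for compliance, so every power figure below rests on an assumption.

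**The plan's own figure.** n = 2(1.96 + 0.84)² × 3.87² / 2.5² = 37.57, so 38 per group. Allowing 20% dropout, 38/0.80 = 47.5, so 48. The stated 48 per group reproduces. The power checks therefore use 38 (completers) and 48 (all randomised).

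**Assumed effect.** d = 2.5/3.87 = 0.646 SD. This is the planning effect for weight, used here for adherence only as an illustration.

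**Full scale.** Power = Φ(d√(n/2) − 1.96).
- n = 38: 0.646 × √19 = 2.816, and Φ(0.856) = 80.4%.
- n = 48: 0.646 × √24 = 3.165, and Φ(1.205) = 88.6%.

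**Two levels, median split, normal data.** The proportions above the cut are Φ(0.323) = 0.627 and Φ(−0.323) = 0.373, a difference of 0.253. Power = Φ[(0.253 − 1.96·SE₀)/SE₁], with SE₀ = √(2 × 0.5 × 0.5/n) and SE₁ = √(2 × 0.627 × 0.373/n).
- n = 38: SE₀ = 0.1147 and SE₁ = 0.1110, giving 60.1%.
- n = 48: SE₀ = 0.1021 and SE₁ = 0.0987, giving 70.5%.

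**Other cuts at d = 0.646** (points lost in brackets):

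| Per arm | Full scale | Median | 30/70 | 20/80 |
|---|---|---|---|---|
| 38 | 80.4% | 60.1% (20) | 54.9% (26) | 47.1% (33) |
| 48 | 88.6% | 70.5% (18) | 65.1% (24) | 56.6% (32) |

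Three levels do not recover the loss. In simulation with cuts near the tertiles, power fell from 79% (t-test) to 60% at 38 per arm, and from 88% to 71% at 48. A continuity correction in the two-level table costs more: the simulated median split at 38 per arm fell from 61% to 52%.

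**Other effects, median split, 38 per arm.** The loss is 8 points at d = 0.3, 14 at 0.4, 18 at 0.5, 15 at 0.8 and 6 at 1.0. It shrinks to about 1 point at d = 1.2, where both analyses are close to 100%.

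**Skewed counts out of 84 days** (beta-binomial, 48 per arm, simulated):
- Mean adherence 85% and 75%, intraclass correlation 0.15: Wilcoxon 89%; chi-square 77%, 70% and 59% with cuts at 90%, 80% and 70% of days. The losses are 12, 19 and 30 points.
- Mean adherence 90% and 80%, intraclass correlation 0.10: Wilcoxon 99%; chi-square 96% with a cut at 90% and 68% with a cut at 70%. The losses are about 4 and 32 points.

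Every scenario showed a loss. Its size depends on inputs that the article does not fix.

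**The case against.** The chi-square sentence states a rule by data type and names compliance levels only as an example. The t-test or Wilcoxon test and the mixed models in the same section are not closed to the day count, and levels could be reported beside days. That stands: a reader might infer that the chi-square is the sole planned analysis of compliance, and the article does not say so. It remains the only test linked to compliance by name, and an analyst following the text would group the count.

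A reader might also infer a general loss of 20 or more power points. The documents do not support that. The 0.65 SD belongs to weight, and the loss is smaller at several other effects and cuts. Nor should the statistical loss be exaggerated: for small effects, a median split of a normal variable keeps about 2/π = 64% of the efficiency.

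The number of levels and the cut-points are details that an article may leave to the full protocol or SAP, so their absence is no fault here.

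Finally, the Abstract's primary and secondary outcomes do not include compliance, and the sample size does not rest on it. The different definitions of an adherent day also mean that a sharper analysis does not by itself make the comparison like for like. Both points stand. They limit the importance and the interpretation of the result, but neither is a reason to group the days.

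**Conclusion.** The point holds as a low-severity, nearly free improvement. Compliance is defined as a number of days, and the one test named for it works on categories, with no reason given for the change of scale. If the adherence difference were about 0.65 SD with roughly normal counts, a median split would cost 20 points of power at 38 per arm (80% to 60%) and 18 at 48 per arm (89% to 71%). Under other plausible effects, cuts and skewed counts the loss is about 4 to more than 30 points, and it vanishes only where the effect is so large that either analysis would detect it. The primary analysis of weight and BMI is unaffected.

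**What to change.** Remove compliance levels from the chi-square sentence and keep that test for data that are categorical as collected, such as adverse-event incidence. Add a sentence along these lines: the number (or percentage) of adherent days over the 12 weeks will be compared between arms on its full scale, by a Wilcoxon test or bootstrap, or by a mixed model of the weekly counts (0 to 7), reporting the between-arm difference with a 95% CI; any table of compliance levels is descriptive.

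State beside it that the difference describes adherence to each arm's own assigned rules, since Table 1 asks for calorie limits alone in the control arm and for eating hours plus calorie targets in the TRE arm.

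The cost is a sentence or two of wording and a little analysis work. The day counts are already collected, and the Wilcoxon test and mixed models are already in the plan.
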